### Data collection methods

After providing informed consent and meeting the eligibility criteria, participants will be enrolled in the study and assigned a unique study identification code, which will be documented in the participants’ records to protect their privacy. After that, they will be invited to complete the baseline assessment. The baseline assessment will include questions on sociodemographic information (eg, date of birth, sex, location, language used at home, education level, current employment status), anthropometric characteristics (eg, weight, height and body mass index), smoking status, comorbid conditions, LBP history (duration, characteristics, pattern of symptoms, surgical history), use of corticosteroids in the past month and the study outcomes.

Baseline and follow-up data collection and management will be performed online via REDCap, using standardised surveys designed to collect data directly from participants via a secure webpage. REDCap is an online, encrypted, customisable data capture tool, hosted by the University of Sydney.^89 90^ Patient-reported outcomes will be collected using valid and reliable self-reported questionnaires (detailed in the Outcomes section). To ensure the completeness of data, participants will receive reminders either via email, SMS or phone call, prompting them to complete a given questionnaire. To minimise missing data, the research team will encourage participants to complete, at a minimum, the primary outcome assessment at the 6-week follow-up assessment. If necessary, completion over the telephone will be made available.

Participants may choose to withdraw at any point. Participants may also choose to stop accessing the app while continuing with some or all aspects of data collection. If a participant withdraws from the study, the nature, timing and reasons for withdrawal will be recorded, and any data provided up to the point of the participant’s withdrawal will be kept in the study records and will be used in statistical analyses, unless the participant specifically requests to withdraw all their data from the study. In this case, their data will be withdrawn, and no attempt will be made to impute missing values for statistical analyses.

### Harms

An adverse event is defined as any undesirable, unfavourable or unintended sign, symptom or disease experienced by a participant in the course of clinical research, which does not necessarily have a causal relationship with the study interventions. A serious adverse event is defined as an unforeseen medical event that occurs in the course of clinical research that results in the participant’s death, is life-threatening to the participant, requires the inpatient hospitalisation or prolongation of existing hospitalisation, or leads to the participant having a persistent or significant disability/incapacity.^91^ This study has been designed to minimise or prevent potential risks. Nevertheless, adverse events are expected and may include flare-ups of LBP, exercise-induced muscle pain, soreness and cramps, unexpected trips and falls, and additional treatments sought for LBP.

Fortnightly, participants will be prompted by email to report the occurrence of adverse events through an Adverse Events Report Form via REDCap during the 6 weeks of intervention and, again, at 52 weeks after randomisation. Participants will indicate any changes in their condition, and the research team will evaluate whether it was related to the intervention or not. When appropriate, participants will be asked to provide further information on whether the adverse event persisted for more than 24 hours and whether medical attention was sought. Participants will be encouraged to contact the research team if they have ongoing or unresolved concerns about the adverse event and its relationship with the study interventions. The research team will monitor reported adverse events until their resolution. Potential harms resulting from participation in the study will not incur any special compensation arrangements. The type of adverse event and the proportions of participants experiencing each event will be reported.

Serious adverse events will be recorded and reported to the Human Research Ethics Committee (HREC) and study sponsor, in accordance with relevant regulatory standards.

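### The serious adverse event definition requires the event to be 'unforeseen', so a serious event of an anticipated type could be classed as non-serious

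*Protocol article*

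**What the plan says.** Everything relevant is in the Harms section of the protocol article.

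- An adverse event is "any undesirable, unfavourable or unintended sign, symptom or disease experienced by a participant in the course of clinical research", whether or not the intervention caused it. Nothing is said about whether it was anticipated.
- For the serious category the wording changes: "A serious adverse event is defined as an unforeseen medical event that occurs in the course of clinical research". Four outcomes follow: death, threat to life, hospital admission ("requires the inpatient hospitalisation or prolongation of existing hospitalisation") and lasting or significant disability.
- The same paragraph then says that "adverse events are expected and may include flare-ups of LBP, exercise-induced muscle pain, soreness and cramps, unexpected trips and falls". The last item on that list is further treatment that participants seek for their back pain.
- On reporting: "Serious adverse events will be recorded and reported to the Human Research Ethics Committee (HREC) and study sponsor, in accordance with relevant regulatory standards". For adverse events in general, "The type of adverse event and the proportions of participants experiencing each event will be reported".

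**The concern.** Seriousness describes the outcome of an event. Expectedness describes whether the event was anticipated. They are normally judged separately, because an anticipated event can still put someone in hospital. Here, being unforeseen is written into the definition of serious, and a few lines later the protocol names event types that it does anticipate. A participant admitted with a flare-up of back pain has a listed serious outcome, but the event is of a type that the protocol foresaw.

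What is at stake is safety oversight. The article describes a route to the ethics committee and sponsor for serious adverse events only, so an event that fails the definition does not enter that route. Two people applying the definition in good faith could also classify the same admission differently, which would make any count of serious events hard to interpret.

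**Working it through.** No arithmetic applies. The check is to apply the definition as written and then look for text elsewhere in the article that overrides it.

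**Step 1. The rule as worded.**

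- Adverse event = any untoward sign, symptom or disease during the research.
- Serious adverse event = unforeseen AND (death OR threat to life OR hospital admission or its prolongation OR persistent or significant disability).

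The second definition is therefore not simply the first plus an outcome. It adds a condition that the first lacks.

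**Step 2. Apply the rule to cases.** *Foreseen* can be read in two ways: by the type of event (is it among those the protocol anticipates?) or by its severity (was an outcome this bad anticipated?). The text does not say which is meant.

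| Case | Adverse event? | Listed outcome met? | Serious, reading by type | Serious, reading by severity |
|---|---|---|---|---|
| Back pain flare-up, no listed outcome | Yes | No | No | No |
| Back pain flare-up, hospital admission | Yes | Yes | **No** | Yes |
| Exercise-induced muscle pain or cramp, any listed outcome | Yes | Yes | **No** | Yes |
| Fall, hospital admission | Yes | Yes | Unclear | Yes |
| Event of a type not named, hospital admission | Yes | Yes | Yes | Yes |

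Rows two and three carry the point: the classification turns entirely on how one adjective is read. Falls are a weak example, because the list itself calls trips and falls unexpected. The list also includes further treatment sought for back pain ("and additional treatments sought for LBP"), so someone could argue that even an admission for back pain was anticipated.

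**Step 3. Follow the consequence.** On the reading by type, the events in rows two and three remain adverse events. They are collected on the same form, followed until resolved, and counted by type and proportion. They do not enter the route described by "Serious adverse events will be recorded and reported to the Human Research Ethics Committee (HREC) and study sponsor".

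**Step 4. Look for an override.** No section says that an anticipated event with a serious outcome counts as a serious adverse event. The reference to regulatory standards in the reporting sentence governs how serious events are recorded and reported. It does not govern which events qualify. The Data monitoring committee and Trial monitoring sections set up oversight but do not define seriousness.

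**The case against.** The strongest reply is that *unforeseen* is a loose adjective and not an exclusion rule. The sentence about expected events follows a statement that the study was designed to keep risk low, and in ordinary English it says only that some adverse events will happen anyway. The article has no formal list of expected events and no rule exempting them. An admission for a flare-up can naturally be called unforeseen in its severity. There are also safeguards: reporting is to follow regulatory standards, the trial committee meets weekly and monitors adverse events, and an independent board reviews accumulating data unblinded. Finally, this is a condensed article, and the report form is not shown.

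Much of this stands. It shows that a sensible reader may well reach the right classification, and it rules out calling the text an explicit exemption. It does not remove the problem, because a definition that has to be rescued by the reader's judgement allows inconsistent classification, and none of the safeguards changes the definition. Nor is this detail left to a fuller document: the definition is stated in the article, and the difficulty lies in a word that is there.

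Two stronger readings should be resisted.

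- **That the safety comparison is tilted in favour of the exercise arms.** The article does not support this. Every participant has chronic low back pain, so flare-ups and extra treatment can occur under control too, and the control arm's education module also guides people towards more physical activity. Four of the five arms receive the exercise module (4/5 = 80% under equal allocation), but that is an allocation share and does not measure misclassified events.
- **That serious harms would go uncollected or unpublished.** They would not. The adverse event definition is broad enough to capture them, and participants are asked, where appropriate, whether they sought medical attention.

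**Conclusion.** The concern holds as a fault in a stated definition. Expectedness has been made a condition of seriousness, next to a list of anticipated event types, and nothing else in the article corrects it. Read literally, a flare-up of back pain or exercise-induced muscle pain with a listed serious outcome could be classed as non-serious and miss the stated route to the ethics committee and sponsor.

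The size cannot be given. There is no event rate, and neither the number of events affected nor the direction of any difference between arms follows from the document. The effect is confined to classification and reporting of serious events. Ascertainment, sample size, the interim decision rules and the primary analysis are unaffected.

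The conclusion rests on two assumptions: that the wording in the article is the wording used to classify events, and that *unforeseen* can reasonably be read as applying to the type of event. If it is always read as applying to severity, the practical effect is small, but the text should say so.

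**What to change.** Delete *unforeseen*. Define a serious adverse event as any adverse event, as this section already defines it, that meets one of the listed outcomes, whether or not it was anticipated. The sentence on anticipated events can stay as background. If expectedness is wanted for reporting, record it separately from seriousness. Relatedness needs no new provision, because the research team already assesses it.

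The Participant timeline section says that recruitment began in June 2024, so events already reported should be re-checked against the corrected definition. Any that meet a listed outcome but were not classed as serious should be reclassified and sent through the stated route.

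The cost is a one-word amendment through the ethics review that the Protocol amendments section already provides for, a short review of existing reports, and possibly a few more events to report.

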### Participant timeline

The study flow chart and study stages are shown in figures1  2, respectively. Study visits and procedures schedule are detailed in table 1. Recruitment has commenced in June 2024.

**Figure 2 F2:**
[figure not shown]
Multi-arm multi-stage design.

**Table 1 T1:** Study visits and procedures schedule

Procedures	Study period and timepoints						
	Screening and Enrolment	Baseline	Allocation	Intervention	Follow-up data collection		
	Week −4 to −1	Week 0	Week 0	Week 1 to 6	Week 6	Week 12	Week 52
Screening and Enrolment							
Informed consent	X						
Eligibility screening	X						
Baseline assessment		X					
Allocation			X				
Interventions							
Control group			X	X	X	X	X
Intervention groups			X	X	X	X	X
Measures							
General characteristics		X					
Primary outcome							
Physical function		X			X	X	X
Secondary outcomes							
Pain intensity		X			X	X	X
Pain frequency		X			X	X	X
Disability		X			X	X	X
Quality of life		X			X	X	X
Sleep quality		X			X	X	X
Consumption of HPF		X			X	X	X
Exercise importance		X			X		
Exercise self-efficacy		X			X	X	X
Adherence to exercise					X		
Co-intervention use		X			X	X	X
Health literacy level		X			X	X	X
Global perceived effect					X	X	X
Impression of change					X	X	X
Overall satisfaction					X		
Usefulness of the app					X		X
Push notifications frequency					X		X
Process measures							
Conversion rate		X					
Recruitment rate					X		
Rate of completed follow-up					X	X	X
Other measures							
Smallest worthwhile effect		X					
Adverse events				X	X		X

X indicates the timepoint(s) when each study procedure will occur.

HPF, highly processed food.

### Sample size

The sample size calculation was conducted a priori, considering a MAMS design with five arms (one control arm and four intervention arms) and two stages that consist of one interim and the final analysis. The primary endpoint was established at 6 weeks post-randomisation (ie, immediate post-intervention). A smallest worthwhile effect on the PSFS score (0–30) of 4 points was chosen to estimate the sample size, considering the literature^76^ and the nature of the intervention (ie, a 6-week digital intervention with no face-to-face interaction).

The sample size calculation was based on a two-sided type I error of 5% (significance level), a power of 80% to control for a type II error and an SD of 5.8 using a generalisation of the power requirements for testing multiple active arms to one control group, as proposed by Dunnett.^92^ The calculation resulted in 21 participants per arm at the first stage and 42 participants per arm at the second stage, reaching a total sample size of 315 participants. Allowing for a loss to follow-up rate of 15% at 6 weeks, the study would require a total sample size of 370 participants (n=25 in the first stage and 49 in the second stage per group). This total sample represents the maximum number of participants that will be enrolled when all the intervention arms meet the criteria for being maintained through the second interim stage (ie, no arm is dropped after the interim analysis). Therefore, there is the possibility that the study terminates with a smaller sample size if, at the interim analysis, one or more intervention arms meet the criteria for being dropped. For instance, if one, two or three arms are dropped after the interim, the study sample will decrease to 321, 272 and 223, respectively.

### Recruitment

Potential participants will be recruited Australia-wide from the community via advertisements published in, but not limited to, internet-based news outlets and newsletters, seniors card newsletters, community lists and social media including Facebook, Instagram, X (formerly known as Twitter) and YouTube. In addition, the George Institute’s Join-Us Research Participant Register (https://www.joinus.org.au/), a secure online register that matches participants with research studies in Australia, will be used.

The advertisements will contain a link or quick response code to the Pre-Screening Questionnaire, available on REDCap, where potential participants can register their interest in the study. REDCap is an online, encrypted, customisable data capture tool, hosted by the University of Sydney. The welcome page will be secured by a Google reCAPTCHA feature, enabled to protect the public survey from abuse by ‘bots’ and prevent automated software programs from submitting fraudulent responses. After passing the reCAPTCHA test, participants will have access to the welcome page and the Pre-Screening Questionnaire.

The Pre-Screening Questionnaire aims to identify potentially eligible participants and collect contact details of individuals interested in the study. Once identified, potentially eligible participants will receive an email with a link to the online Participant Information Statement, containing detailed information about the study and the research team, as well as the contact details for the study, and the Participant Consent Form, both available on REDCap.

The digital divide was an additional layer of complexity that was carefully considered from an equity and inclusivity perspective when designing the study. In the Australian context, critical barriers to digital inclusion include uneven access to networks and digital infrastructure, affordability of devices and data, and a lack of digital literacy and ability, as measured by the Australian Digital Inclusion Index (ADII).^93^ In 2017, Australia was one of the leading adopters of smartphones globally, with 88% of Australians owning one.^94^ In 2023, 99% of Australian adults had Internet access, with 95% of online adults connecting mostly over their mobile phones.^95^ Finally, the 2023 Australian National ADII score was 73.2, with 14.2% and 9.4% Australians classified as digitally excluded and highly digitally excluded, respectively.^93^ Although we do not envisage that a large proportion of the population will be automatically excluded from participating in this study due to digital inequalities, we recognise that this may pose a limitation of the study, with potential impact on recruitment and attrition rates, as well as adherence to the intervention.

### Randomisation: sequence generation, allocation concealment mechanism and implementation

After completing the baseline assessment, participants will be randomly allocated to either the control group or one of the four intervention groups. Computer-generated randomisation will be prepared in permuted blocks of sizes 10–15. To conceal allocation, the randomisation schedule will be generated via a computer, password-protected software by a statistician not involved in participant recruitment, scheduling or assessment. The person who will determine if a potential participant is eligible for inclusion in the trial will be unaware, when this decision is made, to which group the participant will be allocated.

All participants will receive access to the ‘My Back Exercise’ app. However, access to specific intervention components within the app will be available according to the participant’s group allocation, as described next and illustrated in figure 1:

Control group: education module alone.Intervention group 1: education module + educational notifications + exercise module.Intervention group 2: education module + educational notifications + exercise module + sleep module.Intervention group 3: education module + educational notifications + exercise module + diet module.Intervention group 4: education module + educational notifications + exercise module + sleep module + diet module.

After randomisation, participants will receive an email containing detailed instructions on how to download, instal and access the app. This will be followed by a phone call from a member of the research team to help with these procedures if needed, ensure proper functioning of the app and confirm participants only have access to the app components they have been randomly allocated to. Once participants download and instal the app on their own devices, they will receive a welcome email prompting them to access the app and commence the recommended intervention programme. This time point will mark the start of the 6-week intervention programme.

### Blinding

Participants and specific members of the research team (ie, the members of the Data and Safety Monitoring Board (DSMB)) will be unblinded to group allocation. All other research team members, including data collectors conducting baseline and follow-up assessments if required, and data analysts, will remain blinded to group allocation.

As data collection over the telephone will be made available, if necessary, the effectiveness of blinding arrangements will be evaluated at the end of the intervention by asking the assessors to guess the arm to which the participant belonged. Although strategies will be implemented to prevent premature unblinding, breaking of blinding during the study should be expected when this is essential to ensure participant safety. Premature unblinding will be promptly documented and communicated to the study sponsor. The participant will be included in the intention-to-treat analysis in all analyses.

### Data management

All data collection will be performed via REDCap, a secure web application for building and managing online surveys and databases, supported by the University of Sydney. To promote data quality, data collection instruments will incorporate built-in validation features, including branching logic, range checks and required fields, where applicable. Pilot testing of the surveys will be conducted before implementation to ensure proper functioning. In addition, the research team will conduct regular data audits and scrutiny to ensure data quality, integrity, accuracy and completeness. When identified, inconsistencies, omissions or errors will be explored and resolved.

Participant data within the app will be uploaded to the Amazon Web Services, a secure server hosted by Trade eXpansion, the app development team. Appropriate security methods will be implemented to protect the data. Credentials with the right permissions are required, and multi-factor authentication is mandatory. The name of the participant is stored locally on the participant’s phone and is not uploaded to the server.

Digital study data, associated records and study documentation, including confidential data collected from participants, will be exported and stored on the Research Data Store, a password-protected research data storage infrastructure hosted and managed by the University of Sydney, in a re-identifiable (coded) format. Once data collection is completed, identifiers will be removed from the dataset to protect participants’ privacy. Appropriate security methods will be implemented to protect the data by password-protected encryption for digital files.

### Statistical methods

All statistical analyses will be conducted following the intention-to-treat principle. Baseline characteristics will be summarised by arm using descriptive statistics and reported with measures of frequency (proportion), mean, SD and 95% CI. Differences in dichotomous variables will be expressed as risk difference and number needed to treat or number needed to harm with 95% CI. Continuous variables will be summarised and reported with mean and SD in case of a Gaussian (normal) distribution or as the median and IQR in case of a skewed distribution.

At the interim and final analysis, differences in outcome data between each intervention arm and the control group will be analysed using the Student’s t-test in the case of a Gaussian (normal) distribution. Otherwise, the non-parametric Mann-Whitney U test will be used after correcting for baseline differences, if required. Changes in health-related quality of life scores will be analysed using the Wilcoxon test. The Cox proportional hazards regression modelling will be used to adjust for potential confounding factors. For all analyses, statistical significance will be indicated by a p value <0.05.

A planned hypothesis-generating (exploratory) subgroup analysis will be conducted considering diet and sleep. Interaction models will compare the effectiveness of the sleep module in people with low and high scores on the PSQI, as well as the diet module in people with low and high scores on the sQ-HPF. Additionally, a planned exploratory analysis will be conducted to investigate the potential impact of adherence on the magnitude of the treatment effects.

The interim analysis will be conducted after completion of the 6-week intervention programme by the first 25 participants in each arm. Whether and how the trial will continue will be determined by the outcome of the interim analysis, which will allow dropping intervention arms that are deemed futile, in accordance with the following prespecified decision rules considering the primary endpoint (ie, change in mean PSFS score from baseline to 6 weeks after randomisation):

If the change in an intervention arm is no more than 0.5 points greater than the control group, this intervention arm will be dropped. Under this rule, all four intervention arms may be dropped, and the trial terminated. This decision rule was established based on previous adaptive trials investigating conservative interventions in the field of musculoskeletal health.^96^If the change in one intervention arm is more than 4 points higher than the other, the worst-performing intervention arm will be dropped. This decision rule was established considering the smallest worthwhile effect on disability, reported in previous studies as a 15% incremental improvement beyond the natural recovery.^97^ Natural recovery, in turn, is considered a 30% improvement from baseline. Based on our previous study (EMPoweR), a 45% improvement from baseline would correspond to a 5.4-point between-group difference. For this study, this effect size was downgraded to 4 points due to the nature and duration of the intervention (ie, a 6-week digital intervention with no face-to-face interaction).

The decision rules were carefully designed to minimise the risk of prematurely and incorrectly dropping promising treatment arms, potentially leading to a failure to reject the null hypothesis (type II error), while ensuring that the preplanned adaptations would still guarantee increased trial efficiency. Two complementary decision rules were proposed to account for the comparison between each treatment arm against the control group (first rule) and the pairwise comparison among all treatment arms (second rule). Both decision rules are intended to work as indicators of futility, therefore configuring a ‘drop-the-loser’ design that also allows early stopping for futility. Early stopping for efficacy was not planned in this trial.

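### The tests named for the week-6 PSFS comparison make no routine baseline adjustment, which loses precision and leaves a modest bias possible if loss to follow-up depends on baseline function in one arm only

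*Protocol article*

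**What the plan says.** Under Statistical methods, the protocol article commits to the intention-to-treat principle for every analysis ("All statistical analyses will be conducted following the intention-to-treat principle"). For the interim and final comparisons of each intervention arm with control, it says outcome data "will be analysed using the Student’s t-test in the case of a Gaussian (normal) distribution". For other distributions it says: "Otherwise, the non-parametric Mann-Whitney U test will be used after correcting for baseline differences, if required". Baseline therefore enters only in the second branch, and there conditionally. The same section defines the primary endpoint for the interim rules as "change in mean PSFS score from baseline to 6 weeks after randomisation".

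Under Outcomes, PSFS is measured at baseline and at 6, 12 and 52 weeks. Under Randomisation, allocation follows completion of the baseline assessment.

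Under Sample size, the target is "A smallest worthwhile effect on the PSFS score (0–30) of 4 points" with an SD of 5.8, giving 63 evaluable per arm (21 + 42), or 315 in all. The total becomes 370 by "Allowing for a loss to follow-up rate of 15% at 6 weeks".

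Under Data collection methods, data given before a withdrawal "will be kept in the study records and will be used in statistical analyses". The one statement on imputation concerns participants who ask for all their data to be removed: "In this case, their data will be withdrawn, and no attempt will be made to impute missing values for statistical analyses".

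**The concern.** A two-sample test at week 6 needs a week-6 value, observed or imputed. On the score it ignores baseline. On the change it subtracts baseline with a fixed slope of 1, which is not adjustment unless the true slope happens to be 1.

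If the people who remain at week 6 differ in baseline function between the arms, the unadjusted difference carries part of that imbalance into the treatment effect. There is a plausible route to this. Participants know their allocation, and only the intervention arms are asked for 60 to 90 minutes of exercise a week, so poor baseline function could drive loss in those arms and not in control.

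Two things are at stake: a modest bias under that pattern, and a loss of precision whatever the pattern. Both can be avoided with data the trial already collects.

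**Working it through.** **1. The plan's own figures.** 315 / 0.85 = 370.6, against the stated 370 (74 per arm: 25 + 49). In reverse, 370 x 0.85 = 314.5, or 62.9 per arm. The size is thus built on participants with a week-6 score. About 55 of 370 (11 per arm) are expected to lack one, and losing them does not take power below plan.

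**2. Assumptions, not in the documents.** SD 5.8 applies to PSFS at both baseline and week 6, with normal scores. The correlation r between them is 0.3, 0.5 or 0.7. In the intervention arm, loss is 25% in the lower baseline half and 5% in the upper half (15% overall). In control, loss is a random 15%. There is no true effect.

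**3. Baseline shift among those remaining.** Each half's mean lies 5.8 x sqrt(2/pi) = 4.63 points from the centre. Retention is 0.75 and 0.95, so the intervention arm's remaining participants have a baseline mean higher by (0.95 - 0.75) / (0.95 + 0.75) x 4.63 = 0.54 points. The control shift is 0.

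**4. Bias.** On score it is r x 0.54. On change it is -(1 - r) x 0.54.

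| r | Score | Change |
|---|---|---|
| 0.3 | +0.16 | -0.38 |
| 0.5 | +0.27 | -0.27 |
| 0.7 | +0.38 | -0.16 |

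Simulation of the same scenario agrees within Monte Carlo error: +0.16 to +0.39 on score and -0.38 to -0.17 on change. At r = 0.5 it gives +0.28 and -0.27, with 0.00 after baseline adjustment. If both arms lose people in the same way, the 0.54 shift occurs in both and cancels.

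**5. Precision.** The unadjusted standard error is 5.8 x sqrt(2/62.9) = 1.03. At r = 0.5 it is the same for change, because the SD of change is 5.8 x sqrt(2 x 0.5) = 5.8. Adjusted, it is 1.03 x sqrt(1 - 0.5^2) = 0.90. The variance ratio is 0.75, so 63 adjusted participants per arm are worth about 63 / 0.75 = 84 unadjusted ones. This gain does not depend on how people are lost.

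**6. Interim.** An arm is dropped if its change is no more than 0.5 points better than control. With 25 x 0.85 = 21.25 per arm, the standard error is 5.8 x sqrt(2/21.25) = 1.78 unadjusted and 1.78 x sqrt(0.75) = 1.54 adjusted (r = 0.5). For an arm with an assumed true benefit of 2 points, the chance of being dropped is:

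- change, with the bias: Phi((0.5 - 1.73) / 1.78) = about 24.5%
- change, without the bias: Phi(-1.5 / 1.78) = about 20%
- baseline-adjusted: Phi(-1.5 / 1.54) = about 16.5% (16.8% by simulation)

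About half of the gap is precision and half is bias.

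**7. Is a repeated-measures model needed to remove the bias?** In a simulation at r = 0.5 with the same loss pattern, where half of those missing week 6 had a week-12 score, a baseline-adjusted analysis of those with a week-6 score gave bias +0.02 and standard error 0.88. A likelihood model with the later visit and a common baseline mean gave +0.02 and 0.87. In this scenario the remedy is baseline adjustment. Bringing back those without a week-6 score adds little.

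**The case against.** A reader might infer more: that the protocol breaks its own intention-to-treat promise by discarding the planned 15%, and that the discarding causes the bias. The documents do not support this.

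- Intention-to-treat chiefly means analysis by allocated arm. Naming a t-test does not breach it.
- No section says that people without a week-6 score are excluded. The refusal to impute covers only those who withdraw all their data, so imputation for others remains open, and a t-test can follow it. Handling of missing scores is commonly left to the SAP, which is not shown.
- The sentence on retained data concerns what participants gave before withdrawing. It does not promise that a week-12 score will enter the week-6 test, and a withdrawn participant's baseline can still be used in the baseline summaries.
- The calculation in step 7 places the cause in the missing adjustment, not in the absent participants.

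It can also be said that the loss pattern is assumed, that the bias is zero under equal patterns, that on change it runs against the intervention, and that 0.3 points is minor beside an interim standard error near 1.8. All of this stands, and it limits the size of the point. The protocol also plans reminders and telephone completion, which should reduce loss.

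The choice of primary method remains. The article names that method outright and does not leave it to the SAP. The article also names Cox regression for confounder adjustment, but that is a time-to-event model and gives no adjusted PSFS difference.

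**Conclusion.** The point holds as a cheap improvement. It is neither a contradiction within the protocol nor a shortfall in power. The named tests omit routine adjustment for a baseline score that is collected before randomisation.

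Under one assumed pattern (25% and 5% loss by baseline half in the intervention arm, random 15% in control, correlation 0.3 to 0.7), the bias is about +0.16 to +0.39 points on score and -0.38 to -0.17 on change. It is about zero if the arms lose people alike. That is small against 4 points but not negligible beside the 0.5-point futility cut-off. The precision gain at correlation 0.5, from 1.03 to 0.90, holds under either pattern. Its size depends on a correlation that the documents do not give.

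**What to change.** For PSFS and the repeated continuous secondary scores, replace the t-test and Mann-Whitney test with a baseline-adjusted analysis by allocated arm. Either of these would do:

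- ANCOVA of week-6 PSFS on arm and baseline PSFS; or
- a likelihood-based repeated-measures model on baseline, 6, 12 and 52 weeks (arm by visit, common baseline mean, unstructured covariance), including every randomised participant with any score, with the week-6 contrast primary.

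The second also uses partial data, in keeping with the statement on data given before withdrawal. At the interim, apply the existing decision rules to the baseline-adjusted difference. Confirm in the SAP how missing week-6 scores are handled.

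The cost is revised analysis text and a little programming, with no new data or participants. Both options rely on data being missing at random given what is modelled. The unadjusted comparison of those with a week-6 score does not escape this, because it needs a stronger assumption.
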